# Same-visit hepatitis C testing and treatment to accelerate cure among people who inject drugs (the QuickStart Study): a cluster randomised cross-over trial protocol

**DOI:** 10.1136/bmjopen-2023-083502

**Published:** 2024-07-02

**Keywords:** Hepatology, Public health, INFECTIOUS DISEASES

## Abstract

**Introduction:**

Despite universal access to government-funded direct-acting antivirals (DAAs) in 2016, the rate of hepatitis C treatment uptake in Australia has declined substantially. Most hepatitis C is related to injecting drug use; reducing the hepatitis C burden among people who inject drugs (PWID) is, therefore, paramount to reach hepatitis C elimination targets. Increasing DAA uptake by PWID is important for interrupting transmission and reducing incidence, as well as reducing morbidity and mortality and improving quality of life of PWID and meeting Australia’s hepatitis C elimination targets.

**Methods and analysis:**

A cluster randomised cross-over trial will be conducted with three intervention arms and a control arm. Arm A will receive rapid hepatitis C virus (HCV) antibody testing; arm B will receive rapid HCV antibody and rapid RNA testing; arm C will receive rapid HCV antibody testing and same-day treatment initiation for HCV antibody-positive participants; the control arm will receive standard of care. The primary outcomes will be (a) the proportion of participants with HCV commencing treatment and (b) the proportion of participants with HCV achieving cure. Analyses will be conducted on an intention-to-treat basis with mixed-effects logistic regression models.

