### Participant eligibility

Study inclusion criteria for participants are as follows:

Current or former injecting drug use (ie, injected drugs at least once).Aged 18 years or over.Attending a participating primary healthcare for any reason.No previous treatment with DAAs.Medicare eligible.Able to speak and understand English.

Exclusion criteria are as follows:

Women known to be currently pregnant or who are breast feeding.Individuals currently engaged in HCV treatment.Unable to provide informed consent.Tested for HCV in the past 3 months.Previous successful treatment with interferon-based therapy for HCV.

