##### Week 12 (HCV RNA positive)

The study nurse will review the medical records of consented participants to determine whether participants with HCV were provided with a DAA prescription within 12 weeks of enrolment in the study.All participants who have been provided with a DAA prescription will be contacted by the study nurse to ask whether they started treatment and if so, when.

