#### Control arm: SOC testing and treatment

All participants will be tested, treated and followed up according to the usual practice of the clinic for delivery of test results and ongoing HCV treatment. The participants’ medical record will be reviewed at the study close to assess testing and treatment uptake.

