### Study outcomes

The two primary outcomes of this trial include:

The proportion of participants commencing HCV treatment in each arm. Commencement of HCV treatment is defined as receipt of a script for treatment in arms A, B and control and as commencement of treatment with study drug in arm C. The proportion commencing treatment in each intervention arm will be compared with the control arm.The proportion of participants with HCV who start treatment achieving cure. Cure will be assessed by review of medical records for a clinic visit to assess SVR; if no visit has taken place, the study nurse will contact the participant to arrange one in all arms except the control.

Commencing treatment is an important and easily measurable outcome in clinical practice. The rationale for two primary outcomes is that arm C itself involves providing treatment to everyone found to have HCV as part of its intervention.

Secondary outcomes of this study include:

Time to treatment commencement is defined as number of days from first test to first dose of treatment.Case finding is defined as the proportion of people diagnosed with HCV among all those recruited.Cost-effectiveness is defined as the incremental cost to find and commence treatment among one person living with HCV from a health system perspective.

Participant acceptability is based on qualitative evaluation subject to further substudy design and ethical approval.

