### Statistical analysis

Results from the trial will be reported according to the CONSORT extension statement for cluster randomised trials,^38^ or a CONSORT extension statement for cluster randomised crossover trials if one is available prior to end of data collection. Clinic and patient demographics will be described by site and study period. Analyses will be conducted on an intention-to-treat basis, with patients analysed according to the randomised treatment of their cluster at the time of their inclusion in the study. All available binary outcomes will be analysed at the patient level using mixed-effects logistic regression models with random intercepts for clinic and clinic period and fixed effects for interventions.^39^ ORs and 95% CIs will be reported; in addition, we will calculate and report risk differences and 95% CIs.

There are three main comparisons proposed, namely, treatment uptake outcome in arm A versus control (comparison 1) and arm B versus control (comparison 2) and HCV cure in Arm C versus control (comparison 3). Incremental benefits of arm B to arm A, and arm C to arm B, and arm C to arm A on treatment uptake and HCV cure will be performed in subgroup analyses. Data from controls in each arm will be pooled and a single model fitted for each outcome.

Randomisation will occur in batches of six, performed by the coordinating centre and concealed from investigators and sites until after site governance approcal. Since randomisation is occurring within batches of six services, fixed effects for batch will be included in these models. The Kenward-Roger correction will be applied to adjust for the small number of clinics.^40^ Estimates of intracluster correlations (within-period and between-period) will be reported. Time-to-event outcomes such as time to complete diagnosis will be analysed using Cox proportional hazards models with shared-frailty terms for site and fixed terms for treatment group and randomisation batch. There may be imbalances between sites with respect to various clinic and patient-level characteristics, and secondary analyses will adjust for these.

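### Primary outcome 1 has two different denominators; if it means participants with HCV, who is counted depends on each arm's own testing pathway

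*Protocol article*

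**What the plan says.** The Protocol article describes the denominator of treatment uptake in different ways.

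- Abstract, Methods and analysis: "the proportion of participants with HCV commencing treatment".
- Week 12 (HCV RNA positive), under arms A and B: records are reviewed "to determine whether participants with HCV were provided with a DAA prescription within 12 weeks of enrolment in the study".
- Study outcomes: "The proportion of participants commencing HCV treatment in each arm", without mention of HCV status. The rationale below it speaks of arm C treating everyone in whom HCV is found.
- Sample size: expected uptake of 30%, 50%, 70% and 90% in control, A, B and C, applied to counts of recruited participants (24, 30 or 40 per site per period, at most 2400 in all).

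HCV status need not be known at entry: a criterion is "Attending a participating primary healthcare for any reason", and people tested in the past 3 months are excluded. Arms A, B and C begin with a study rapid antibody test. For control, "All participants will be tested, treated and followed up according to the usual practice of the clinic", and the "medical record will be reviewed at the study close to assess testing and treatment uptake". A secondary outcome covers diagnosis: "Case finding is defined as the proportion of people diagnosed with HCV among all those recruited". The Statistical analysis section says "Analyses will be conducted on an intention-to-treat basis", by the allocation of the cluster at the time of inclusion.

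**The concern.** The 30% to 90% rates and the week-12 checks make sense only for people with HCV, so that is the likelier intention. But the article gives no way to classify an infected control participant who is never tested. That person cannot be counted as having HCV and drops out of the denominator, while a similar person in arms A to C has been offered a test on the day. The comparison then conditions on a step that follows randomisation and that the intervention is meant to change.

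The article itself gives reasons to expect a difference. The Introduction names repeated venepuncture for diagnosis as a barrier and cites a study in which more people completed screening with a point-of-care test. Two of the three main comparisons (A versus control and B versus control on uptake) are exposed. The best-worst and worst-best analyses vary missing treatment status; they do not clearly address unknown HCV status.

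**Working it through.** **1. The plan's own figures.** Significance level: 0.05/3 = 0.0167. Inflation for loss: 24/(1 − 0.20) = 30. Maximum: 5 sites × 6 sequences = 30 sites; 30 × 2 periods × 40 = 2400. All reproduce.

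Power for 30% versus 50% (24 per cluster-period, 10 clusters) is stated as above 80%. The article gives no intracluster correlation (ICC) or cluster autocorrelation (CAC), so I used a range:

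Var = (2s²/m) × [1 + (m − 1)·ICC − m·ICC·CAC]/K, with s² = (0.30 × 0.70 + 0.50 × 0.50)/2 = 0.23, m = 24, K = 10, two-sided alpha 0.0167, noncentral t on 8 df.

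| ICC | CAC | Power |
|---|---|---|
| 0 | any | 0.91 |
| 0.01 | 0.8 | 0.89 |
| 0.05 | 0.8 | 0.85 |
| 0.10 | 0.8 | 0.78 |
| 0.05 | 0.5 | 0.73 |

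The stated power is attainable and is not shown to be wrong, but it treats all 24 as contributing to the outcome.

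**2. Effect of the denominator.** Let π be HCV prevalence among recruits, t the share of infected people tested and diagnosed, and u the share of those diagnosed who commence treatment (subscript 0 for control, A for arm A). Uptake is u among the diagnosed, t·u among all infected and π·t·u among all recruited; case finding is π·t. None of π, t and u is in the article. The values below are assumptions: π = 0.30, t₀ = 0.60, t_A = 0.90, u = 0.50 in both arms.

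| Denominator | Control | Arm A | Difference |
|---|---|---|---|
| Diagnosed | 50% | 50% | 0 |
| All infected | 0.60 × 0.50 = 30% | 0.90 × 0.50 = 45% | 15 points |
| All recruited | 0.30 × 0.60 × 0.50 = 9.0% | 0.30 × 0.90 × 0.50 = 13.5% | 4.5 points |
| Case finding | 0.30 × 0.60 = 18% | 0.30 × 0.90 = 27% | 9 points |

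The all-infected difference minus the diagnosed-only difference is u₀(1 − t₀) − u_A(1 − t_A). Here that is 0.50 × 0.40 − 0.50 × 0.10 = 0.15. Other assumed cases:

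- t = 0.60 v 1, u = 0.50 in both: 0 points among diagnosed; 30% v 50% among all infected, which is the plan's own planning effect.
- t = 0.80 v 1, u = 0.375 v 0.50: 12.5 points among diagnosed; 20 points among all infected.
- t = 1 in both, u = 0.30 v 0.50: 20 points on either denominator.

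If testing is equal but incomplete, the all-infected difference is t(u_A − u₀), which is no larger than the diagnosed-only difference, so again nothing is hidden.

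**3. Power when recruits are not all infected.** Same formula, ICC 0.05, CAC 0.8, 24 recruited per cluster-period, everyone infected being found. The with-HCV analysis uses m = 24π; the all-recruited analysis keeps m = 24 with rates 0.30π v 0.50π.

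| Assumed prevalence | With HCV | All recruited |
|---|---|---|
| 30% | 36% | 20% |
| 40% | 47% | 28% |
| 50% | 57% | 38% |
| 70% | 71% | 58% |

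For example, at 40%: m = 9.6 for the with-HCV analysis, and 12% v 20% for all recruited.

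**The case against.** The strongest reply is that incomplete control testing is inferred. The sentence on the control arm opens by saying that all participants will be tested, and no rate is given anywhere. That stands as far as size goes. But the same sentence ties testing to usual practice, and the next one has testing uptake read from records, so complete testing is not assured.

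The contrast between arms is also less sharp than a test on the day suggests. In arms A and C, RNA is confirmed on a venous laboratory sample, and arm A participants with a negative rapid result may decline confirmation. This stands, and it is why the illustration uses 90% for arm A and not 100%. The illustration also fixes uptake after diagnosis as equal, which removes any effect of rapid results on linkage to care; it is a deliberately stark case.

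Infection at enrolment is a baseline trait, and the article defines intention-to-treat as analysis by cluster allocation, so a with-HCV analysis is not in itself a breach. The difficulty is only that status may be ascertained differently by arm.

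An all-recruited proportion has a weakness of its own: unblinded clinic staff approach participants, so any between-arm difference in the HCV prevalence of those recruited enters it directly. This stands as a limit on the remedy.

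Finally, analysis-set rules may sit in the statistical analysis plan, which the Data monitoring section describes as under development. That excuses missing detail, but not an outcome described two ways in one document.

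**Conclusion.** The denominator of primary outcome 1 is inconsistent within the article and should be settled. If it is participants with HCV, comparisons 1 and 2 can be biased wherever control testing is less complete, usually by overstating control uptake; in the assumed example a 15-point difference among all infected people appears as zero among the diagnosed.

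A reader might infer more: that uptake is definitely measured only in people found to have HCV, that control uptake is bound to be inflated relative to the intervention arms, and that the benefit of testing is missed entirely. The documents do not support this. The Study outcomes definition carries no HCV restriction. Testing rates are unknown, and the direction can change with how ready for treatment the people diagnosed in each arm are. Case finding among all recruited would still show the gain in diagnosis, so the loss would be to the primary comparison and not to the trial.

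The sizes rest on assumed prevalence, testing and uptake, and the power figures on an assumed ICC of 0.05 and CAC of 0.8.

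**What to change.** 1. State one denominator for outcome 1, in the same words, in the Abstract, Study outcomes and Sample size sections.
2. Beside the with-HCV analysis, prespecify an all-recruited intention-to-treat analysis in the same mixed model: laboratory RNA-positive and commenced treatment = yes; everyone else, including the untested = no. Apply the same RNA-positive rule in arm C, so that presumptive dosing of RNA-negative people does not count as uptake.
3. Interpret comparisons 1 and 2 together with that analysis and with case finding.
4. State that the planning power applies to participants with HCV, and restate it with an assumed HCV prevalence among recruits.

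The cost is one further model on data already collected, a revised sample-size paragraph and agreed wording. The all-recruited analysis has clearly lower power (about 20% to 58%, against 36% to 71%, over the prevalence range above) and is open to differential recruitment. It should therefore support the with-HCV analysis and not silently replace it.

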**Ethics and dissemination:**

The study has been approved by the Alfred Ethics Committee (number HREC/64731/Alfred-2020-217547). Each participant will provide written informed consent. Reportable adverse events will be reported to the reviewing ethics committee. The findings will be presented at scientific conferences and published in peer-reviewed journals.

**Trial registration number:**

NCT05016609.

**Trial progression:**

The study commenced recruitment on 9 March 2022 and is expected to complete recruitment in December 2024.

STRENGTHS AND LIMITATIONS OF THIS STUDYThe QuickStart Trial will recruit from a focused population, people with current or past history of injecting drugs, who are most at risk of hepatitis C.A cross-over clustered randomised control trial design will be used to increase study power by leveraging within-site comparisons.Four study conditions will be investigated to analyse three rapid point-of-care (POC) testing and treatment interventions, compared with a control arm; one arm investigates a rapid POC antibody test and same-day treatment—an intervention that could be used in resource-limited settings if found to be effective.Medical record review will be used in addition to in-person participant follow-up to monitor study outcomes and reduce loss to follow up.The participant recruitment strategy counteracts several biases present in observational studies, but participation is voluntary, so a risk of selection bias remains.

## Introduction

As of 2019, approximately 58 million people worldwide were living with hepatitis C virus (HCV), causing around 290 000 deaths annually.^1^ In Australia, approximately 118 000 people were living with HCV at the end of 2020.^2^

Direct-acting antiviral medications (DAAs) are highly effective (cure rates >90%), have minimal side effects and require only 8–12 weeks of daily tablets. The Australia Pharmaceutical Benefits Scheme is a government programme that subsidises medicines to improve affordability.^3^ In 2016, the Pharmaceutical Benefits Scheme negotiated a fixed-price contract providing access to DAAs for every Australian living with HCV, giving Australia a unique opportunity to eliminate HCV.^4 5^

Most untreated HCV infections in Australia are among people with a history of injecting drug use.^2 6^ Models of HCV epidemics where transmission is driven by injecting drug use suggest that treating people who inject drugs (PWID) and people with a history of injecting drugs will lead to substantial reductions in HCV incidence and liver-related morbidity and mortality.^7–9^ Indeed, models have shown that treating as few as 6% of the estimated population of PWID in Australia annually for 10 years would reduce new HCV infections by 80% and HCV prevalence in PWID by 10%.^10 11^ However, in Australia, PWID remain underdiagnosed, undertreated and underserviced in HCV care and healthcare more broadly.^2 12–14^

Unrestricted access to DAAs following government subsidy in 2016 resulted in an initial spike in treatment uptake due to increased availability of the medication to those who had previously been unable to access it. However, treatment numbers have since declined, exacerbated by the COVID-19 pandemic.^2 15 16^ There exist service, provider and individual barriers to accessing HCV care.^17^ One service-related barrier among PWID is the current need for multiple venepunctures in order to be diagnosed with HCV in Australia, particularly as venous access can be challenging in PWID.^18 19^ Current clinical guidelines and funding rules require specific assessments before treatment can be started^20^ necessitating multiple clinic visits. Data from the Australian Needle and Syringe Programme Survey estimates that among the 93 000 PWID in Australia, the majority (89%) had a lifetime history of HCV antibody testing.^21^ However, individuals are gradually lost throughout the cascade of care. Of Australian Needle and Syringe Programme Survey participants reporting testing positive for an HCV antibody test, only 32% reported accessing HCV treatment up to 2020 (prior to the COVID-19 pandemic).^22^

Point-of-care (POC) HCV testing can simplify the diagnosis of HCV in healthcare settings. The emergence of rapid POC testing for both HCV antibodies and RNA has made this feasible. The OraQuick rapid HCV antibody test is self-contained and uses fingerstick capillary blood samples to provide results in around 20 min. The GeneXpert HCV Viral Load test detects HCV RNA using fingerstick capillary blood to provide results in around 60 min. These tests have been shown to be highly sensitive and specific,^23 24^ and overcome many of the barriers to treatment associated with the conventional care model.

Studies suggest POC testing is acceptable among PWID and can be feasibly integrated into health services.^19 25–27^ However, limited data have assessed the impact of POC testing on treatment uptake. One study in France found a larger proportion of individuals who received a POC test completed HCV screening and were linked to care compared with those with standard serological testing.^28^ Provisional data in Australia found POC testing through needle and syringe exchange programmes reduced time to treatment.^29^ In Connecticut, patients selecting POC testing were more likely to be linked to HCV treatment than those opting for standard laboratory testing.^30^ These studies suggest that POC testing has a positive effect on retention in HCV care.^27 29^ Beyond rapid testing, the feasibility of same-day testing and treatment with DAAs has been demonstrated: preliminary studies have shown high levels of linkage to care following same-day testing and treatment.^31^ Same-day testing and treatment have also been shown to achieve high cure rates compared with facilitated referral.^32^ However, only a limited number of studies have assessed the impact on retention in care of same-day treatment following POC testing for HCV.^31^

From these existing data, there are broadly three rapid testing models of care being contemplated and deployed in real-world settings: first, POC antibody testing alone (corresponding to arm A of QuickStart Trial, more fully defined below); second, combined POC antibody and RNA testing (arm B); and third, combined POC testing and same-day treatment (Arm C). While promising in pilot studies, none of these models have been tested formally in clinical trials. Clinical trial evidence is required to determine the effectiveness of POC testing with or without treatment compared with the current standard of clinical care.

The QuickStart Trial will first determine the effectiveness of rapid POC testing in primary healthcare settings on treatment uptake. We hypothesise that rapid antibody testing alone (arm A), and rapid antibody followed by immediate RNA testing (arm B), will increase treatment uptake compared with standard clinical care (the control arm). Second, QuickStart will determine the effectiveness of POC antibody testing followed by same-day treatment (Arm C) on cure. We hypothesise that testing and same-day treatment will increase cure compared with standard clinical care. Our secondary outcomes will also compare each of the three intervention models to each other for any incremental benefit on treatment uptake and cure.

## Methods and analysis

### Trial design

A clustered randomised cross-over trial with six treatment sequences will evaluate the effects of rapid POC testing on retention of participants with HCV care and achievement of cure. Each site will have a standard of care (SOC) control period randomly occurring before or after one of three intervention arms, allowing for intrasite comparison. Each site will have an SOC control period randomly occurring before or after one of the three intervention arms, allowing for intrasite and intersite comparisons to be combined in the estimation of treatment effects. The cross-over design has advantages in ensuring that any external changes that occur over time can be accounted for, which a simple before and after intervention comparison would not allow. External changes might occur at the clinic level, such as services and staff becoming more aware or skilled in offering HCV testing, or they may occur at a system level, such as changes in access to testing, care or treatment. There will be a 1-month washout period between arms at each study site. Participant recruitment began in March 2022 and is intended to continue for up to 24 months.

